##### Non-invasive markers of fibrosis

Changes in our secondary outcome measures over 90 days up to maximal 360 days as per schedule (table 1), these include: serum enhanced liver fibrosis (ELF) test (iQur, London, UK, serum Protein Fingerprint markers (Nordic Bioscience, Herlev, Denmark), hepatic TE (Echosens, Paris, France) and the UK End-Stage Liver Disease (UKELD) score.

**Table 1 T1:** Trial assessment schedule

	Visit 1a	Visit 1b	Treatment group				Control group					
			Visit 2a Within 7±4 days of Visit 1b	Visit 2b 7>10 days after apheresis (Day 0)	Visit 2c (Day 7)	Visit 2d (Day 14)	Visit 2 (day 7±4 days from visit 1b)	Visit 3 (Day 28*±4* days)	Visit 4 (Day 56*±4* days)	Visit 5 (Day 90*±7* days)	Visit 6 (Day 180*±7* days)	Visit 7 (Day 360*±7* days)
Informed consent	X											
Clinical assessment	X	X	X	X	X	X	X	X	X	X	X	X
Vital signs	X	X	X	X	X	X		X	X	X	X	X
Screening blood tests	X											
ECG	X											
Standard blood tests	X	X		X	X	X		X	X	X	X	X
Research bloods*			X		X	X	X	X	X	X	X	X
Mandatory microbiology	X		X									
Ferritin	X			X†	X	X						
Triglyceride	X			X†	X	X						
Pre-infusion blood tests				X								
MELD/UKELD	X	X		X	X	X		X	X	X	X	X
Pregnancy test	X‡	X‡		X‡	X§							X‡
Abdominal Ultrasound Scan (USS)	X¶										X¶	X¶
Fibroscan	X									X	X	X
ELF panel	X							X	X	X	X	X
Protein fingerprint	X¶							X¶		X¶		
CLDQ		X								X	X	X
31P MRS MRI**	X*									X		
Adverse events	X	X	X	X	X	X	X	X	X	X	X	X
Clinical events	X	X	X	X	X	X	X	X	X	X	X	X
Concomitant Medication	X	X	X	X	X	X	X	X	X	X	X	X

*If pass screen and before visit 2b.

†Obtain before discharge.

‡women of child bearing age only.

§If test not carried out at previous visit.

¶Fasted visit.

**Royal Infirmary of Edinburgh (RIE) patients only.

CLDQ, Chronic Liver Disease Quality of Life Questionnaire; ELF, enhanced liver fibrosis; MELD, Model for End-Stage Liver Disease; MRS, MR spectroscopy; UKELD, UK Model for End-Stage Liver Disease.

##### Enhanced liver fibrosis

A standardised clinically validated immunoassay test measuring three serum biomarkers which have been shown to correlate to the level of liver fibrosis assessed by liver biopsy, comprising:

Hyaluronic acid.Tissue Inhibitor of Metalloproteinase 1.Aminoterminal propeptide of type III procollagen.

The concentrations of each individual protein marker are combined in an algorithm which produces a composite score related to the level of liver fibrosis. The ELF score is a sensitive, specific and validated method for the non-invasive assessment of hepatic fibrosis in mixed, HCV and NAFLD patient groups.^28^

##### Protein Fingerprint biomarkers

During extracellular matrix (ECM) turnover, proteolytically cleaved matrix degradation fragments or neoepitopes, are released into the systemic circulation. Cleavage of each ECM protein by specific MMPs generates a unique neoepitope. These neoepitopes are more accurate diagnostic and prognostic markers for individual fibroproliferative diseases than their protein of origin. These novel serum biomarkers have been shown to identify patients with progressive fibrosis and permit monitoring of the response to antifibrotic therapy,^29^ and also correlate with portal hypertension in patients with cirrhosis.^30^

##### TE (Fibroscan)

TE is a non-invasive method for assessing liver fibrosis. Mild amplitude and low frequency vibrations (50 Hz) are transmitted to the liver tissue, inducing an elastic shear wave that propagates through the underlying liver tissue. The velocity of the wave is directly related to tissue stiffness, considered as a surrogate of the amount of fibrotic tissue. This is expressed as a numerical value in kilopascals (kPa). It is reliable, reproducible with high intraobserver and interobserver agreement and has been validated in most causes of chronic liver disease^31^

##### Chronic Liver Disease Quality of Life Questionnaire

The Chronic Liver Disease Quality of Life Questionnaire (CLDQ) is a liver-specific questionnaire for measuring HRQoL in participants with chronic liver disease. It is self-administered, takes approximately 10 min to complete and is designed to reflect the 2 weeks prior to testing. If necessary, participants can request help to complete this.^32^

It includes 29 items divided into 6 quality of life domains: Abdominal symptoms, Fatigue, Systemic symptoms, Activity, Emotional function and Worry. These items are ranked on a 1–7 scale, providing a possible range of scores from 29 (worst quality of life) to 203 (best quality of life). The construct validity of the CLDQ was supported by a strong correlation with participant’s global rating scores. It has been shown to be valid and has good test–retest reliability.^33–35^

##### UKELD score

The UKELD score is readily performed incorporating routine biochemical and haematological indices including bilirubin, albumin, alanine transaminase (ALT) and International Normalised Ratio (INR). The UKELD score was developed by the UK Liver Transplant Units to predict transplant waiting list mortality.^36^

The score uses the parameters of Bilirubin (Bil), INR, Creatinine (Creat) and Sodium (Na) in the following algorithm:

UKELD= [(5.395*ln(INR))+(1.485*ln(Creat)+(3.130*ln(Bil))-(81.565*ln(Na))]+435

##### MRI and MR spectroscopy

MRI and spectroscopy (MRS) provide methods for the non-invasive assessment of liver microstructure and function. MRI allows for imaging biomarkers to be determined using Liver*Multi*Scan.^37^ Tissue microstructure will be investigated using clinically validated metrics. Fibrosis will be assessed by cT_1_, iron content with T_2_* and the amount of fat in the liver using proton density fat fraction. Organic phosphorus in the liver can be quantified with Phosphorus-31 (^31^P) MRS^38^ a more explorative technique. Using ^31^P MRS energy metabolism may be investigated via ATP levels and cell membrane integrity by measuring precursors and degradation products. The paired imaging of this study allows for the current utility of MRI to assess disease progression and treatment response to be evaluated

MRI data collected is exploratory and will be according to subgroup analysis: the only planned subgroup analysis is to present the primary outcome for the RCT by disease aetiology (ALD, NAFLD, other). MRI is performed at index visit 2 (or within 7 days) and again at primary outcome time point of 90days (±7).

### Sample size/power calculation

To detect a difference in the baseline to 90-day change in MELD score of 1 SD using a two-sided, two-sample test with a 5% level of significance, a sample size of 23 per group to detect the same level of difference with 90% power is required. All analyses will be carried out on an intention to treat basis, retaining participants in their randomised treatment groups irrespective of the treatment received. Adverse event (AE) data will be presented by treatment received.

The number of participants who do not adhere to the protocol is expected to be low. All protocol violations and ineligible participants will be recorded.

### Recruitment

#### Identification of potential patients

Potential participants will be identified by their usual direct healthcare team. The treating physician will either introduce the individual to the trial team or ask permission for the trial team to contact them; this could be done through a dedicated invitation letter or a telephone call. The participant information sheet will be provided and there will be an opportunity to ask questions. If they agree, a further visit will be scheduled to discuss trial enrolment. This will take place no less than 24 hours later.

#### Randomisation

Following confirmation of the participant meeting the eligibility criteria, a delegated member of the research team will enter minimal information (participant id, and aetiology) into an online randomisation system, produced for the study by Edinburgh Clinical Trials Unit to determine the treatment allocation. At randomisation, patients will be allocated a unique patient trial number and scheduled for treatment and follow-up visits as detailed in the trial schedule.

#### Allocation

Participants will be assigned to receive either standard medical care or to receive a fresh dose of autologous MDMs at the maximum achievable dose, in a 1:1 ratio based on a minimisation algorithm using the key variable aetiology of disease (ALD, NAFLD, other.) To ensure the allocation is random, participants will be assigned to the group which minimises the imbalance with probability 0.8. If a participant falls into two or more strata, then the dominant aetiology (as determined by treating physician) will be used.

#### Blinding

Due to the nature of the intervention neither participants nor staff can be blinded to allocation of treatment. For some of the additional secondary outcomes we will maintain blinding of external assessors including those processing samples for ELF and protein fingerprint markers. Similarly, there is blinding of MRI physicists and external validation companies responsible for experimental MRI interpretation.

### Data collection

The case report form (CRF) will be completed at set time points as per trial schedule. The CRF will be completed by the investigator or an authorised member of the research team (as delegated on the Site Signature and Delegation Log). The exception is the serious AE Form which must be signed by the investigator.

Data reported in each form should be consistent with the source data or the discrepancies should be explained. If information is not known, this must be clearly indicated in the form.

Completed CRFs submitted to the clinical research facility will be reviewed by the trial coordinator. The data will be entered into an electronic database by designated members of the trial team.

### Data management

The following personal data will be collected as part of the research: name, date of birth and CHI numbers (Community Health Index; a unique is a 10-character numeric identifier, allocated to each patient on first registration with the NHS system in Scotland). Personal data will be stored in locked cabinets by the research team at the clinical research facilities at each site. Personal data will be stored for 30 years in keeping with the blood safety and quality regulations. The University of Edinburgh and NHS Lothian are joint data controllers along with any other entities involved in delivering the study that may be a data controller in accordance with applicable laws.

All investigators and study site staff involved with this study must comply with the requirements of the appropriate data protection legislation (including where applicable the general data protection regulation regarding the collection, storage, processing and disclosure of personal information. Access to personal information will be restricted to individuals from the research team treating the participants, representatives of the sponsor(s) and representatives of regulatory authorities.

Study data will be collected and managed using Research Electronic Data Capture (REDCap) electronic data capture tools hosted at The University of Edinburgh. REDCap^39^ is a secure, web-based application designed to support data capture for research studies, providing: an intuitive interface for validated data entry; audit trails for tracking data manipulation and export procedures; automated export procedures for seamless data downloads to common statistical packages; and procedures for importing data from external sources.

Published results will not contain any personal data that could allow identification of individual participants.

### Statistical analysis plan

The baseline to 90-day change in MELD score will be compared in the two treatment arms using a two-sample t-test or non-parametric equivalent as appropriate. MELD scores calculated for each participant throughout the trial will be used to calculate an area under the curve (AUC) and this will be compared across the groups using a two-sample t-test or non-parametric equivalent as appropriate. In the event of varying durations in the trial follow-up, the average AUC per month will be used so that all participants have a comparable measurement.

Changes in secondary outcome measures (ELF score liver stiffness, CLDQ score, transplant-free survival, number of clinical events, UKELD score, blood parameters (bilirubin, albumin, ALT, INR)) over the 1-year study period will be presented graphically by dose. Similarly, these results will used to calculate an AUC for each participant and will be compared across the groups using a two-sample t-test or non-parametric equivalent as appropriate.

The only planned subgroup analysis is to present the primary outcome by disease aetiology (ALD, NAFLD, other). Primary data analysis will be conducted on participants who receive a single infusion versus control; the primary analysis will then be repeated to include those subjects who receive more than one infusion (three individuals). There are no plans for an interim analysis.

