### Trial design

The MATCH trial is designed as a multicentre, open-label, parallel-group, phase 2, RCT to compare autologous macrophage therapy with standard medical care in patients with compensated cirrhosis. Randomisation will be performed with a 1:1 allocation ratio and the primary outcome is the baseline to 90-day change in Model for End-Stage Liver Disease (MELD) score. Figure 1 provides an overview of trial pathway following randomisation to the respective arms. Initially, the proposed trial was designed to administer three infusions to those randomised to the treatment arm. It became apparent that it would not be acceptable or feasible to continue with three infusions due to the onerous commitment required of participants and the challenge to complete the trial within the proposed time frame. Therefore, as a pragmatic approach, and in line with the phase 1 study, it was decided that a single infusion protocol should be adopted to simplify the participant journey and ensure adequate recruitment. This was agreed with the trial steering committee (TSC), sponsor and data monitoring committee (DMC).

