### Interventions

Participants who are randomised to the treatment arm will receive an infusion of the maximum achieved dose up to 1×10^9^ (day 0). The apheresis product will be collected under the terms of the Human Tissue (Quality and Safety for Human Application) Regulations 2007 No. 1523 enacting the requirements of the EU Tissues and cells Directive (2004/2023) and associated Commission Directives at the Apheresis Unit (Royal Infirmary of Edinburgh, Edinburgh, UK). CD14+ monocytes will be isolated, and the macrophage cell product will be manufactured as previously described,^25^ in compliance with GMP regulations under the terms of the SNBTS MIA (IMP) licence at the SNBTS Cell Therapy Facility (Scottish Centre for Regenerative Medicine, Edinburgh, UK).

Each patient will be monitored closely during the infusion to identify potential hypersensitivity reactions and 4 hours postinfusion bloods to monitor for any evidence of macrophage activation syndrom. A total of 28 participants will be randomised to standard medical care and 28 to receive the cell infusion, allowing for original estimate of 5 dropouts from each arm. Additional safety data will be collected for the first infusion only for the first three patients randomised to the treatment arm. If it has not been possible to achieve 1×10^9^ macrophages, then the participants will be infused with the quantity obtained, with minimum concentration being 1.25×10^8^ cells. This minimum cell concentration was derived from previous validation work and is stipulated as part of the product release criteria as designated by the MHRA.

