#### Secondary outcome measures

##### Transplant-free interval

The number of participants in each of the two treatment arms who are transplant free at 12 months will be expressed as proportions and a binomial test will be used for the comparison of proportions between the treatment arm and the control arm. The difference in proportions will be presented along with the 95% CI for the difference in the proportions.

The time to death or transplant will be presented using a Kaplan-Meier survival curve stratified by treatment and accompanied by a log-rank statistic comparing the two arms. Survival estimates with be presented by treatment arm at 3, 6, 9 and 12 months.

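### The primary test on day-90 MELD change can use only participants with a day-90 value and ignores baseline MELD, aetiology and the earlier visits, so precision is lost and uneven dropout can bias it

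*Protocol article*

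**What the plan says.** Under Trial design, "the primary outcome is the baseline to 90-day change in Model for End-Stage Liver Disease (MELD) score". The Statistical analysis plan section says: "The baseline to 90-day change in MELD score will be compared in the two treatment arms using a two-sample t-test", or a non-parametric equivalent where that is suitable. It names no covariates. The same section compares a MELD area under the curve between arms, averaged per month where follow-up varies, but as a separate comparison.

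Under Sample size/power calculation, the target is a 1 SD difference in the 90-day change, two-sided 5%, 90% power, 23 per group. Under Interventions, 28 per arm are randomised, "allowing for original estimate of 5 dropouts from each arm".

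Two statements define who is analysed. Sample size/power calculation applies intention to treat to all analyses, "retaining participants in their randomised treatment groups irrespective of the treatment received". The Statistical analysis plan section says "Primary data analysis will be conducted on participants who receive a single infusion versus control", followed by a repeat that adds the three participants with more than one infusion.

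Table 1 schedules MELD at Visits 1a and 1b for everyone, at days 0, 7 and 14 in the treatment arm only, and at days 28, 56, 90, 180 and 360 (read here as common to both arms). Aetiology is the only minimisation factor (Allocation). Death and transplant are analysed as a secondary outcome: "The time to death or transplant will be presented using a Kaplan-Meier survival curve".

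**The concern.** A two-sample test on change from baseline to day 90 can use only participants who have both values. Someone who leaves after day 56 has two post-baseline MELD scores on file, and the primary test uses neither. Up to 10 of 56 participants are planned to be lost in this way.

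The trial is open label, and only one arm undergoes apheresis and infusion, so dropout may well differ between arms. If those who leave are also those who are worsening, the arm with more dropout looks better than it is.

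Apart from bias, subtracting baseline is less efficient than adjusting for it. A comparison that ignores the minimisation factor also forgoes whatever precision aetiology offers. With about 23 analysed per arm, neither loss is negligible.

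**Working it through.** **1. The plan's own figure.** Inputs: difference 1 SD, two-sided 5%, 90% power. The normal formula gives n = 2(1.960 + 1.282)² / 1² = 21.02, so 22 per group. The exact t-test needs 22.02, so 23. The stated 23 is reproduced; power at 23 per group is 91.2%. Then 28 − 5 = 23, and planned loss is 10/56 = 17.9%. With purely random dropout of about 5 per arm, simulated power is 91.1% and there is no bias. The sample size is therefore sound if dropout is random.

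**2. Bias from uneven dropout.** Suppose k of n participants leave an arm, and their day-90 change would have been worse than the arm mean by D. The mean of those remaining is then too favourable by k·D/(n − k).
- 5 of 28 lost: 5/23 = 0.217 × D.
- 2 of 28 lost: 2/26 = 0.077 × D.
- 5 versus 0 therefore gives 0.217·D. With the same D in both arms, 5 versus 2 gives 0.140·D. It is somewhat less if the first to leave are the most extreme.

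Two sets of simulations put a size on this. All inputs on correlation and dropout pattern are assumptions, since the article gives none.

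| Dropout mechanism (no true effect) | 5 v 2 lost | 5 v 0 lost |
|---|---|---|
| Driven by worsening already seen at day 56: bias of the change-score test | 0.18 points | 0.35 points |
| Driven by the day-90 change itself plus noise: bias | 0.12 SD | 0.22 SD |
| Same mechanism: false-positive rate (5.2% with no loss) | 9.5% | 13.5% |

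By the formula, 0.35 points at 5 versus 0 corresponds to D = 0.35 × 23/5 = 1.6 MELD points. In the first row a repeated-measures model removes the bias, because the day-56 values carry the information. In the other two rows it would not remove all of it, because loss depends on a value nobody observes.

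**3. Precision.** With equal variance σ² at both times and correlation ρ, the change score has variance 2σ²(1 − ρ). The baseline-adjusted outcome has σ²(1 − ρ²). The ratio is (1 + ρ)/2, which is below 1 for any ρ below 1.
- ρ = 0.5: 0.750, standard error 13% smaller.
- ρ = 0.65: 0.825, 9% smaller.
- ρ = 0.73: 0.865, 7% smaller.
- ρ = 0.8: 0.900, 5% smaller.

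The 7 to 9% reduction found by simulation therefore matches a baseline to day-90 correlation of about 0.65 to 0.73. At that level 23 per arm does the work of 23/0.865 = 26.6 to 23/0.825 = 27.9 per arm, roughly what the dropout allowance gives up.

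**4. Death and transplant by day 90.** The Introduction gives 4.4% one-year mortality in compensated disease. At a constant hazard, 56 × (1 − 0.956^(90/365)) = 0.62 deaths are expected, with a 46% chance of at least one. No transplant rate is given, and listed patients are excluded at entry.

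If one transplanted participant among 23 were scored with a MELD fall of 3 to 9 points, the arm mean would move by 3/23 = 0.13 to 9/23 = 0.39 points. That is 0.04 to 0.26 SD for an assumed SD of change of 1.5 to 3. With a true 1 SD effect and one such event in the control arm, t-test power lies between 61% and 90% for falls of 2 to 7 points and SDs of 1.5 to 4.

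**5. Power of a worst-rank analysis** (true 1 SD, 23 per arm): about 90% with no events; 92% and 94% with one and two control events; 80% and 66% with one and two treated events; 86% with one in each arm. With 28 randomised per arm, 3.1% events and 14.8% dropout, it is 84%.

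**The case against.** The strongest objection is that a journal article commonly leaves rules for missing values, death and transplant to the full protocol or analysis plan. Neither is shown, so their absence here is not an error. That stands.

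It also disposes of a stronger reading that a reader might infer: that the plan as written scores a transplant as an improvement and discards deaths. The article says neither. The intention-to-treat sentence concerns allocation versus treatment received; it is not a rule for scoring MELD after a transplant. Inflating 23 to 28 is ordinary allowance for dropout, which is consistent with a completers' analysis but does not prescribe one.

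A second objection is that the plan permits a non-parametric test and uses early MELD values in the area under the curve. Neither repairs the primary test. A rank test on observed changes still needs a day-90 value. The area under the curve is a different quantity, and it does not feed into the day-90 comparison.

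A third objection is that the proposed model has its own assumption, that loss is explained by observed data. That is true, but the assumption is weaker than that of the change-score test, which uses none of the post-baseline data of those who leave.

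**Conclusion.** The point holds as a criticism of the stated method. An unadjusted comparison of day-90 change, powered on 23 of 28 per arm, loses precision in any case: about 7 to 9% of the standard error at correlations near 0.65 to 0.73, and 5 to 13% over 0.8 to 0.5. If dropout is related to liver function and uneven between arms, it is also biased. The estimate is 0.18 to 0.35 MELD points at 5 versus 2 and 5 versus 0 dropouts when loss follows day-56 worsening. If dropout is random, or balanced with the same pattern in both arms, no systematic bias is expected.

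Death and transplant are a secondary matter. About 0.6 deaths are expected among 56 participants by day 90, and transplants should be few. Any claim that a transplant is counted as benefit must stay conditional on what the full documents say. The power losses above are ranges over assumed values, because the SD of MELD change, the correlations, the transplant rate and the dropout pattern are not in the article.

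**What to change.** Make the primary analysis a repeated-measures model on MELD at days 28, 56 and 90 in all randomised participants, adjusted for aetiology and for a baseline MELD taken before randomisation in both arms. Read the treatment difference at day 90. The day 0, 7 and 14 values exist only in the treatment arm and should not enter. Reconcile the intention-to-treat sentence with the sentence limiting the primary analysis to single-infusion recipients versus control, so that one analysis set is named.

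As a safeguard, state that MELD after a transplant is not scored as improvement. Add a pre-specified sensitivity analysis in which death or transplant before day 90 takes the worst rank. This matters because the model treats values after death as merely missing.

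The cost is analysis-plan wording and slightly more analysis work, with no new visits, data or participants. The model still assumes that missingness is explained by observed data. The rank analysis loses about 1 to 2 points of power if no events occur; otherwise its power rises or falls with the arm in which they occur.

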## Eligibility criteria (inclusions/exclusions)

### Inclusion criteria

Aged between 18 and 75 years (inclusive) at time of screeningAetiology: One or more of:Alcohol-related liver disease (no active alcohol misuse ≥6 calendar months prior to screening). Features of chronic liver disease with a compatible history of alcohol excess (>80 g/day), in the absence of other causes of chronic liver disease.PBC 2 out of: Cholestatic liver function tests (LFTs), Positive antimitochondrial antibody (titre >1:40). Compatible liver histology (if already receiving ursodeoxycholic acid must be established on current dose >3 months prior to enrolment).NAFLD Either: Histological evidence of hepatic steatosis in the absence of other liver diseases Or: Imaging compatible with NAFLD (eg, fatty infiltration of liver) and one or more risk factors (eg, elevated body mass index, type 2 diabetes mellitus, hypertriglyceridaemia, hypertension) and the absence of significant alcohol consumption (<20 g/day) and no evidence of other causes of chronic liver disease.Cryptogenic cirrhosis diagnosis of cirrhosis unattributable to any other cause.Haemochromatosis diagnosis made on basis of compatible biochemistry (transferrin saturation >60%, ferritin >400), genotype (homozygous C282Y or H63D compound heterozygote) or histology.Alpha-1 antitrypsin deficiency diagnosis based on compatible genetic, phenotypic or histological testing.Previous chronic hepatitis C (sustained viral response ie, undetectable HCV RNA 24 weeks after treatment).Diagnosis of cirrhosis—invasive or non-invasive criteria cirrhosis defined as any of:Biopsy-confirmed diagnosis of cirrhosis.Transient elastography (TE)—≥15 kPa.Clinical and radiological features which in the opinion of the investigator correlate with a diagnosis of cirrhosis.A MELD score (Pre-2016) of ≥10 and ≤17 at screening visit.

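### The primary test is an unadjusted t-test on MELD change; adjusting for both scheduled pre-treatment MELDs (Visits 1a and 1b) would gain precision at almost no cost

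*Protocol article*

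**What the plan says.** The Trial design section states that "the primary outcome is the baseline to 90-day change in Model for End-Stage Liver Disease (MELD) score". The Statistical analysis plan section gives the test: "The baseline to 90-day change in MELD score will be compared in the two treatment arms using a two-sample t-test". A rank-based alternative is allowed where suitable. Neither section names a baseline covariate, and nowhere does the article say which visit supplies baseline or how many readings go into it.

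The MELD/UKELD row of Table 1 is marked at Visit 1a and Visit 1b, in the columns common to both arms. It is blank at Visit 2a (treatment) and Visit 2 (control), and marked at Visit 2b, which is day 0 and exists only for the treatment group. Later MELDs include day 90. So every participant has two scheduled readings before apheresis or infusion, and treated participants have a third before infusion.

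The Inclusion criteria require "A MELD score (Pre-2016) of ≥10 and ≤17 at screening visit". Visit 1a, with consent and screening bloods, appears to be that visit.

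The Sample size/power calculation section plans "To detect a difference in the baseline to 90-day change in MELD score of 1 SD". The planned test is two-sided at the 5% level, and the section concludes that "a sample size of 23 per group to detect the same level of difference with 90% power is required". The Interventions section randomises 28 per arm, allowing for 5 dropouts in each.

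**The concern.** A change score gives the baseline reading a fixed coefficient of one, whatever its actual relation to the day-90 value. If baseline is one reading, its whole short-term variation enters the change, while the other scheduled pre-treatment reading is unused. A model that estimates the coefficients of both readings can remove variance that the t-test leaves in.

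The trial is small, so precision matters: 23 evaluable participants per arm carry the primary test. Both readings are already scheduled, so using them needs no extra visit, sample or participant.

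The open choice of baseline visit adds a lesser reason to settle this. The last pre-treatment MELD is Visit 2b in one arm and Visit 1b in the other, so a rule based on the last value before treatment would draw on different visits in the two arms.

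**Working it through.** **1. The plan's own figure.** Inputs from the Sample size/power calculation section: difference 1 SD of the change, two-sided 5%, power 90%, equal groups. The normal approximation gives 22 per group; the noncentral t solution is 22.02, rounded up to 23. Power is 89.97% at 22 and 91.25% at 23 (44 degrees of freedom). 23 + 5 = 28. The stated figures reproduce.

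**2. Variances.** The article gives no MELD SD and no visit correlations, so what follows rests on assumption. Set the variance of MELD to 1 at each visit. Let r be the correlation of either pre-treatment reading with day 90, and q the correlation between Visits 1a and 1b.

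- Change from one reading: 2(1 − r)
- Change from the mean of 1a and 1b: (1 + q)/2 + 1 − 2r
- Linear model, one reading as covariate: 1 − r²
- Linear model, both readings as covariates: 1 − 2r²/(1 + q)

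The planned effect is 1 SD of the change from one reading. Under another analysis it becomes √(variance of that change ÷ new variance).

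Example, r = 0.7 and q = 0.85. Change from one reading: 0.600. Change from the mean: 0.925 + 1 − 1.4 = 0.525, ratio 0.875. One covariate: 0.510, ratio 0.850. Two covariates: 1 − 0.98/1.85 = 0.470, ratio 0.784, so the effect is 1/√0.784 = 1.13 SD.

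Variance ratio to the change from one reading, with power at 23 per arm (44, 43 and 42 degrees of freedom in turn):

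| r | q | mean of 1a and 1b | one covariate | two covariates |
|---|---|---|---|---|
| 0.5 | 0.50 | 0.750, 96.9% | 0.750, 96.9% | 0.667, 98.2% |
| 0.5 | 0.95 | 0.975, 91.9% | 0.750, 96.9% | 0.744, 97.0% |
| 0.7 | 0.70 | 0.750, 96.9% | 0.850, 94.9% | 0.706, 97.6% |
| 0.7 | 0.85 | 0.875, 94.4% | 0.850, 94.9% | 0.784, 96.3% |
| 0.7 | 0.95 | 0.958, 92.3% | 0.850, 94.9% | 0.829, 95.3% |
| 0.8 | 0.80 | 0.750, 96.9% | 0.900, 93.8% | 0.722, 97.4% |
| 0.8 | 0.95 | 0.938, 92.9% | 0.900, 93.8% | 0.859, 94.7% |

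**3. Cost of the covariates.** Going from 44 to 42 degrees of freedom with no variance gain changes power from 91.25% to 91.19%. Estimating two coefficients also means correcting for chance imbalance. For normal covariates this multiplies the variance of the arm difference, on average, by 1 + 2/(44 − 2 − 1) = 43/41 = 1.049. With no gain at all, power would then be 89.9%. The last column of the table becomes 93.7% to 97.7%.

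**4. Range when MELD drifts between 1a and 1b.** The table assumes that both visits correlate equally with day 90. If instead MELD moved as pure drift without reading error, the best prediction of day 90 would be the Visit 1b value itself and Visit 1a would add nothing, so the gain would be zero. Simulations under assumed variances, allowing drift, gave a residual variance 0.2% to 29% below that of the unadjusted change from 1b. That converts to power of 91.2% to 97.6% at 42 degrees of freedom, or 89.9% to 97.0% after the factor 43/41.

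**5. Why not simply average.** Let r_a and r_b be the correlations of 1a and 1b with day 90. Averaging gives a larger variance than 1b alone when r_b − r_a > (1 − q)/2. With r_a = 0.7, r_b = 0.8 and q = 0.85, the left side is 0.10 and the right side 0.075. The change from the mean has variance 0.925 + 1 − 1.5 = 0.425, against 2(1 − 0.8) = 0.400 for 1b alone, an increase of 6%. The two-covariate model gives 1 − (0.49 + 0.64 − 2 × 0.56 × 0.85)/(1 − 0.7225) = 0.359, a reduction of 10%. In the simulations with drift, averaging ran from about a 27% reduction to about a 5% increase. Before the cost in step 3, the linear model cannot do worse than either change score, since each is a special case with fixed coefficients (0 and 1, or ½ and ½).

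**The case against.** The strongest reply is that nothing here is wrong. An unadjusted comparison of changes between randomised arms is valid. The planned effect is expressed in SDs of that change, so its noise is already in the calculation, and the stated 90% is met. How baseline is derived from repeated readings is ordinary content for the full protocol or analysis plan, which are not shown. All of this stands, and an undefined baseline is not counted here as a defect. What remains is that the article does fix the primary test, and a better one is available from the same data.

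A reader might infer more, in four ways that the article does not support:

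- That the change is taken from a single MELD. The text never says so; it is only the natural reading.
- That selection on MELD 10 to 17 biases the result through regression to the mean. Selection precedes randomisation and acts on both arms alike.
- That the day-0 MELD is being used as baseline in the treatment arm. Table 1 makes this possible but does not state it.
- That the trial has no reserve because 22 per arm gives less than 90%. The shortfall is 0.03 percentage points, and 28 per arm are randomised.

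It is also fair to say that one covariate captures much of the gain: 93.8% to 96.9% in the table. The second reading adds from almost nothing to a few points.

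**Conclusion.** The point holds as an efficiency improvement. It is neither a bias nor an error in the stated power. Two pre-treatment MELDs are scheduled in both arms, and the stated primary test does not adjust for either.

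At 23 per arm and the planned 1-SD effect, the two-covariate model moves power from 91% to between about 91% and 97%. The most favourable corner of the table, where the two pre-treatment readings correlate at only 0.5, reaches 98%. If the readings add almost nothing, the full cost of the covariates leaves about 90%. These figures rest on assumed variances and correlations. The table further assumes equal variances at the visits, which selection on the screening MELD would disturb. The article gives no data with which to narrow the range.

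The two-covariate form is preferred to averaging because it does not depend on MELD being stable between Visits 1a and 1b.

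**What to change.** State the primary analysis as a linear model for day-90 MELD with treatment arm, Visit 1a MELD and Visit 1b MELD as covariates. Using the change as outcome gives the same arm estimate once both readings are in the model. Where a single baseline value is needed, for example to describe the change or draw a plot, take Visit 1b in both arms and not Visit 2b. Eligibility stays on the screening reading.

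The cost is a few lines in the analysis plan, two degrees of freedom and the small imbalance charge shown above; no visit, sample or participant is added. Because the trial is open-label, fix the choice before outcome data are examined by arm. The unadjusted t-test can be kept as a sensitivity analysis.
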